#### Eligibility

The following criteria are used to check eligibility for participation in the trial:

Completion of a curative-intent treatment for cancer at least 3 months ago (checked by participant’s medical doctor). For this study, surgery, chemotherapy, radiotherapy, immunotherapy, and/or stem cell transplantation are considered treatment. However, hormonal therapy, the use of anti-inflammatories, and monitoring visits are not considered treatment for this study.Patient has been suffering from severe fatigue for at least 3 months.Patient scores 35 or higher on the fatigue severity subscale of the Checklist for Individual Strength (CIS).Aged 19 years old or older.At least 18 years old at disease onset.Capable of reading and writing in the Dutch language and of using the Internet (implicit eligibility criterion accounted for during registration, but not checked explicitly).

If patients meet 1 or more of the following criteria, they are excluded from participation:

Indication of current disease or tumor activity (checked by the participant’s medical doctor).Current or former severe psychiatric morbidity, for example, major depression, psychosis, or schizophrenia (checked by the participant’s medical doctor).Being dependent on a wheelchair for daily activity (self-report).Recurrence of cancer during the course of the study (self-report).Current substance abuse, except for smoking.Previously attended the eMBCT of the Helen Dowling Institute.

In addition to the mentioned exclusion criteria, please note that:

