### Outcome Measures

#### Fatigue

Fatigue severity will be assessed with the CIS, which consists of 20 items that score on a 7-point Likert scale [53,54]. The CIS has 4 subscales (fatigue severity, motivation, concentration, and physical fatigue) of which the fatigue severity subscale will be used as the primary outcome (8 items, range: 8-56 points). The CIS has shown good discriminative validity in a working population [55], is sensitive to changes in the chronic fatigue syndrome population [56], and has previously been used with cancer survivors [7,57]. The CIS strongly resembles the Multidimensional Fatigue Inventory, which is often used in international studies [54]. Fatigue severity will be assessed at T0a, T0b, M3, M6, M9, T1, T2, and T3. However, the other 3 subscales will only be assessed at T0b, T1, T2, and T3.

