#### Core Analysis

##### Effectiveness

###### Overview

Five steps will be taken to evaluate the effectiveness of both interventions, which are explained here in a generic way. The specific hypotheses on the effectiveness of the interventions in our study are shown in Textbox 1.

Hypotheses on effectiveness.
*Primary outcome*
In both experimental conditions:Fatigue severitydecreases during the intervention, andremains decreased after 6 months.After 6 months, fatigue severity has decreased significantly more compared to the control condition.After 6 months, more participants show a clinically relevant reduction of fatigue severity compared to the control condition. A patient is considered clinically improved if he or she has a reliable change index of more than 1.96, according to the reliable change index, and the end score has to be within the normal range, that is a score < 1 standard deviation above the mean of a normative group [94] (ie, a score < 30.4 on the CIS fatigue severity subscale [51]).
*Secondary outcomes*
For both interventions we expect that:After 6 months, mental health and work ability have improved more than in the control condition.After 12 months, fatigue severity, work ability, and mental health remain improved in both intervention groups.Improvements in mental health and work ability after 6 and 12 months are related to reductions in fatigue severity.Return to work and reduced absenteeism will be studied as explorative outcomes.

###### Step 1

Overall effectiveness will be tested in an intention-to-treat analysis by a multiple group latent growth model [79] using data from the first semester. This technique allows individuals to have an individual growth trajectory over time and compensates for missing data in an elegant way.

Since different growth patterns are expected for the pre-intervention period, the intervention period, and the post-intervention period, we will apply piecewise growth modeling so that a slope factor will be estimated for each of the 3 periods (Figure 4). Initial intercepts will be configured to represent the T0b score. This intercept and the pre-intervention slope factor will be constrained to be equal between all 3 conditions (and this assumption will be checked), whereas the subsequent slope factors will be estimated separately for the 3 conditions.

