The fit of the piecewise model will be compared with a quadratic model. In the quadratic model, the entire first semester is modeled with 1 slope factor and 1 quadratic factor for each of the 3 conditions and an intercept that represents T0b and is constrained similarly to the piecewise model.

Both models will be run both with and without using time-varying loadings in order to check whether corrections should be made for differences in timings between the questionnaires. Growth factor estimates and model fits for all 4 models will be reported (Table 5).

Neither the participants nor the researchers ([name] and MW) are blinded to allocation. Therefore, an independent statistician ([name]) who is blind to the allocation will test the primary hypothesis.

The same procedure will be followed for the secondary outcomes, except that the initial intercept of mental health will represent T0a, rather than T0b, because T0b does not include an assessment of mental health.

Results of frequentist analyses will be reported by *P*-values (significant in case <.05) and with 95% confidence intervals. Parameter estimates of models by means of Bayesian estimators will be reported with 95% central credibility intervals.

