**Figure 4 figure4:**
[figure not shown]
Simplified representation of a piecewise linear latent growth model, with latent intercept factor (I), latent slope factors preintervention (S(pre)), during the intervention (S(int)), and postintervention (S(post)), and 7 indicators Y. Error terms, correlation coefficients, and covariances are left out.

**Table 5 table5:** Growth factor estimates of 4 different latent growth models.

	Fixed loadings	Time-varying loadings
Piecewise, linear	Mean: I, S(pre), S(int), S(post) Variance: I, S(pre), S(int), S(post)	Mean: I, S(pre), S(int), S(post) Variance: I, S(pre), S(int), S(post)
Quadratic	Mean: I, S, Q Variance: I, S, Q	Mean: I, S, Q Variance: I, S, Q

###### Step 2

The effect size of both experimental interventions will be calculated according to recommendations in Feingold (2009) [95] for both primary and secondary outcomes.

###### Step 3

The proportion of participants who make clinically relevant progress on the primary outcome will be calculated for all 3 conditions; again, in an intention-to-treat analysis. Percentages and standard deviations of the reliable change index will be presented.

###### Step 4

A latent growth model will be built of the primary outcome, in which the outcome measures that have been measured at T3 will also be included, as distal outcomes of changes in the primary outcome during the first semester.

###### Step 5

A growth mixture model (GMM) will be used to further explore differences between individuals, and more specifically to identify subpopulations (latent classes) with homogeneous growth trajectories of the primary outcome within the experimental groups. The Bayesian information criterion will be used for model selection [96].

If convergence considerations allow, this model will be adjusted to allow covariance of the growth factors in order to acknowledge individual variation around the estimated growth trajectories. The trace plots will be inspected to check whether the models have converged to global solutions and a set of diverse starting values will be used. For more information on these analyses, we refer to an introduction to GMM and latent class growth analysis by Jung and Wickrama [97] and examples of similar analyses in the field of Internet interventions [98] and cancer patients [41].

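### Step 1's quadratic comparator has no common pre-intervention slope, so it appears to fit arm-specific curves through the eligibility score; if relied on, it shrinks effects that arise during treatment

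*Protocol article*

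**What the plan says.** Step 1 (Core Analysis, Effectiveness) plans a piecewise latent growth model because "different growth patterns are expected for the pre-intervention period, the intervention period, and the post-intervention period". In that model, "This intercept and the pre-intervention slope factor will be constrained to be equal between all 3 conditions"; only the later slopes differ by arm.

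Its fit is then compared with a quadratic model, in which "the entire first semester is modeled with 1 slope factor and 1 quadratic factor for each of the 3 conditions", with "an intercept that represents T0b and is constrained similarly to the piecewise model". Table 5 lists for the quadratic model only "Mean: I, S, Q Variance: I, S, Q", with no S(pre).

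The Figure 4 caption gives the piecewise model three slope factors "and 7 indicators Y". Under Outcome Measures, Fatigue: "Fatigue severity will be assessed at T0a, T0b, M3, M6, M9, T1, T2, and T3". The Design section makes T0a the eligibility check. The Eligibility section requires at least 35 on this same subscale, and the Randomization section places allocation after T0b. Step 8 extends whichever model is final in Step 1 and provides for a quadratic slope.

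**The concern.** T0a is measured before allocation, so the arms cannot differ there in expectation. The piecewise model respects this through the common pre-intervention slope. A quadratic curve with its own slope and curvature in each arm, tied together only at T0b, does not: the same two terms that describe the arm's course after randomization also have to describe the step from T0a to T0b.

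Two things follow. First, when the arms separate during the intervention, the equal T0a means pull the arm-specific terms together and shrink the estimated difference. Second, everyone was selected for a high T0a score, so the mean falls from T0a to T0b by regression to the mean, and the curve carries part of that fall into the treatment period. The first touches the between-arm hypothesis at 6 months. The second touches the within-arm hypothesis that fatigue falls during the intervention.

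**Working it through.** **Which scores enter.** The listed fatigue assessments without T3 (12 months, outside the first semester) are T0a, T0b, M3, M6, M9, T1 and T2. That is 7, which reproduces the Figure 4 count. Without T0a there are 6, and nothing before T0b from which to estimate S(pre). So T0a is in the piecewise model. For the quadratic model, inclusion is inferred: it covers the whole first semester, and a comparison of fit needs the same indicators in both models.

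**Algebra.** With a common intercept at T0b (t = 0), the arm difference is D(t) = ΔS·t + ΔQ·t². At T0a, g weeks earlier, D(−g) = −g·ΔS + g²·ΔQ. The true value is 0, which requires ΔS = g·ΔQ. An effect that rises early and levels off needs ΔS and ΔQ of opposite sign, so the condition fails and the fit compromises by shrinking the difference. An effect that builds late can meet it.

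**Assumptions (none is given in the documents).** Between-person SD 7, occasion SD 5, applicant mean 40, entry at T0a ≥ 35, g = 2, 4 or 8 weeks. Assessments at weeks 0, 3, 6, 9, 11 and 26 from T0b. True effect 5 points, no true change in controls. Large-sample means and covariance were fitted by GLS with a common intercept and arm-specific S and Q.

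| True course of the effect | 6-month difference with T0a in the quadratic model (g = 2 / 4 / 8) | Loss against 5 |
|---|---|---|
| Complete by week 9, then held | 4.57 / 4.21 / 3.93 | 9% / 16% / 21% |
| Half by week 9, half after | 4.80 / 4.65 / 4.55 | 4% / 7% / 9% |
| Linear to 6 months | 4.88 / 4.79 / 4.74 | 2% / 4% / 5% |
| Starts only after T1 | 4.99 / 5.08 / 5.17 | none |

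For the held effect, the quadratic model without T0a gives 5.05 at 6 months. Against that reference the losses are 10%, 17% and 22%, hence about 9 to 22% overall. At week 9 the held effect is estimated as 3.91 / 3.08 / 1.97 with T0a and 4.67 without. The step from 5 to 4.67 is quadratic misfit and has nothing to do with T0a; the remainder is a loss of 16% / 34% / 58% against 4.67.

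**Regression to the mean.** Expected T0a-to-T0b fall = (σₑ²/σ)·φ(z)/(1−Φ(z)), with σ = √(49+25) = 8.60 and z = (35 − mean)/σ.
- Mean 40: z = −0.58, 28% of applicants fail the cut-off, and the fall is 2.91 × 0.469 = 1.4 points.
- Calibrated to the Results section: 60% of 50 exclusions is 30, and 30/(50 + 111) = 19%. This needs a mean near 42.5 (z = −0.87), and the fall is 2.91 × 0.338 = 1.0 points.

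The fitted week-9 change in an unchanging control arm is −0.72 / −0.70 / −0.57 (mean 40) or −0.49 / −0.49 / −0.40 (mean 42.5), and about 0 without T0a.

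**Second calculation.** Maximum likelihood with random slopes, a 4-point effect held from week 10, applicant mean 40 and the protocol's expected 94/77/77 at T2 gives:
- 6-month differences of 3.71 / 3.39 / 3.12, that is 7% / 15% / 22% too small, with power 0.94 / 0.90 / 0.85. The piecewise model gives 4.08 and 0.97.
- With no treatment effect (g = 4), an estimated between-arm difference of −0.02.
- At g = 2 or 4, −2 log-likelihoods of 7927.8 (quadratic) and 7927.1 (piecewise). The quadratic model has 7 mean parameters (I, 3 S, 3 Q) against 8 (I, S(pre), 3 S(int), 3 S(post)). At g = 8 the figures are 7936.8 and 7927.1.

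**Check of the remedy (held effect, GLS).** A quadratic model with a common S(pre) gives 5.04 at 6 months and 4.65 at week 9. Dropping T0a gives 5.05 and 4.67. The spurious control change is at most 0.02 points either way.

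**The case against.** The best reply is that the quadratic model is only a comparator. Step 1 commits to the piecewise model, holds intercept and pre-slope equal across arms and checks that assumption. Estimates and fit for all four models are to be reported, so a discrepancy would show, and the responder proportions in Step 3 do not use the growth model. This stands: harm needs the quadratic model to be chosen or leaned on. Step 8 allows for that choice, and under short gaps fit would hardly separate the two models.

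Nor does any sentence place T0a in the quadratic model, and the seven indicators caption the piecewise figure. That also stands, so the point is conditional on the natural reading. If T0a was meant to be left out, the two fits are not comparable as described and the text should say so.

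A reader might infer more, which the documents do not support:
- That the arms are forced apart at T0a whenever they differ later. The algebra shows otherwise for late effects, so shrinkage toward zero is not universal.
- That regression to the mean threatens the randomized comparison. All arms are selected alike, and it cancels.
- That the fit comparison is itself distorted. On the same indicators it is valid, and misfit at T0a counts against the quadratic model; it may simply have little power to discriminate.

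The held-effect scenario is also close to the worst case at 6 months, and the large week-9 losses bear on no stated between-arm hypothesis.

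**Conclusion.** The point holds in conditional form. As written, the quadratic comparator lacks the common pre-intervention slope that protects the piecewise model, and it most naturally runs arm-specific terms through the eligibility score. If it becomes the final Step 1 model or is read as confirmation, the 6-month difference is understated for effects that arise during the intervention: by about 9 to 22% if complete by week 9 and held, the pattern nearest the protocol's own hypothesis of a decrease that is then maintained, and by about 2 to 9% if gradual. There is no loss for effects that start after T1. A spurious within-arm fall of roughly 0.4 to 0.7 points at week 9, on a scale of 8 to 56, would help to satisfy the within-arm hypothesis without any true change.

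These sizes rest on assumed SDs, gap, applicant mean and effect. The direction is firm for early effects; the magnitude is not. It should be corrected, but it does not undermine the planned piecewise analysis.

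**What to change.** Add one sentence to Step 1, choosing one of two options, and amend Table 5 to match.
- Give the quadratic model a single pre-intervention slope held equal across the 3 arms, with arm-specific S and Q starting at T0b. T0a then enters both models in the same way. Cost: one more parameter.
- Use T0a for eligibility only and drop it from both models, together with S(pre), so that they are compared on T0b, M3, M6, M9, T1 and T2. Cost: a small loss of baseline precision.

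Either needs only a refit and no new data.

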#### Mental Health

Mental health will be assessed from the results of 2 questionnaires: the Positive and Negative Affect Scale (PANAS [52]) and the HADS [58], both of which are included in an item bank for cancer survivors [59]. The PANAS consists of 20 items that score on a 5-point Likert scale and has 2 subscales: positive and negative affect. The HADS consists of 14 items on a 4-point scale, has been validated for a Dutch-speaking population [60], and has previously been used to assess psychological distress in cancer patients [61]. Mental health will be assessed at T0a, T1, T2, and T3.

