#### Perceived Ability to Work

The work ability score, which is assessed with the first question of the work ability index [62,63], will also be used as an outcome parameter. It asks: “Imagine that your working ability in the best period of your life is rated 10 points. How would you rate your working ability at the present moment?” It is assessed at T0b, T1, T2, and T3.

Working hours and the level of absenteeism are assessed with questions from the Trimbos and iMTA questionnaire on costs associated with psychiatric illness (TiC-P) [64]). These will be assessed at T0b, T2, and T3.

**Table 2 table2:** Assessments of outcome measures and potentially mediating factors.

Outcome Measures and Potentially Mediating Factors		Parameters	T0^a^	Mi/Mi’^b^	T1/T1’	T2/T2’	T3
Primary outcome	Fatigue severity	CIS fatigue severity subscale: 8 items on a 7-point Likert scale.	a, b	3,6,9	x	x	x
Secondary outcomes	Other dimensions of fatigue	CIS physical and cognitive fatigue and motivation subscales: 4 items for each subscale, all on a 7-point Likert scale.	b		x	x	x
	Affect	PANAS: 20 items on a 5-point Likert scale.	a		x	x	x
	Psychological distress	HADS: 14 items on a 4-point scale.	a		x	x	x
	Self-perceived ability to work	Work ability score: 1 item on a 0-10 numeric rating scale (NRS).	b		x	x	x
	Return to work and working hours	Adapted questions of the TiC-P.	b			x	x
Primary mediating factors	Mindfulness	Freiburg Mindfulness Inventory short form [65,66]: 14 items on a 4-point Likert scale.	b	3,6,9	x	x	x
	Physical activity (PA)	Accelerometer: ProMove 3D [52]. Both summative PA and daily PA decline will be considered.	b	3,6,9^c^	x		
	Sleep quality	Subjective Sleep Quality Scale [67]:15 items (yes/no), and 1 self-conceptualized item (yes/no) that translates into: “Did you use sleep medication?”	b	3,6,9	x	x	x
	Sense of control over fatigue	Self-Efficacy Scale [56]: 7 items on a 4-point Likert scale.	b	3,6,9	x	x	x
	Credibility and expectancy	Credibility and Expectancy Questionnaire [68]: 6 items of which 4 are on a 9-point Likert scale, and 2 items on a 0-100 NRS.	c, c’	1,2,4			
	Working alliance	Working Alliance Inventory short form [69,70]: 12 items on 5-point scale; subscales: goal, task, bond.		1,2,4			
Secondary mediating factors	Perceived physical activity	Four self-conceptualized questions on perceived activity volume, comparative volume, and satisfaction with volume.	b		x	x	x

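### Step 1 carries the primary outcome's growth models over to secondary outcomes with only three first-semester occasions, too few to estimate those models as specified with fixed loadings

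*Protocol article*

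**What the plan says.** Step 1 under Effectiveness fits a multiple-group latent growth model "using data from the first semester". In the piecewise version "a slope factor will be estimated for each of the 3 periods" (before, during and after the intervention). The intercept and pre-intervention slope are held equal over the three arms, and the later slopes are free. The quadratic version has an intercept, a slope and a quadratic factor. Each version is run with fixed and with time-varying loadings, and estimates and fit are to be reported for all four. For the piecewise row, Table 5 lists "Mean: I, S(pre), S(int), S(post) Variance: I, S(pre), S(int), S(post"), so the factors are random. The Figure 4 caption says that error terms and covariances are only omitted from the drawing.

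For the secondary outcomes the instruction is: "The same procedure will be followed for the secondary outcomes, except that the initial intercept of mental health will represent T0a, rather than T0b". No other exception is given.

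The assessment schedule differs by outcome. For the primary outcome: "Fatigue severity will be assessed at T0a, T0b, M3, M6, M9, T1, T2, and T3". For HADS and PANAS: "Mental health will be assessed at T0a, T1, T2, and T3". For the work ability score: "It is assessed at T0b, T1, T2, and T3". The other three CIS subscales follow the same schedule as work ability.

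**The concern.** A growth model needs enough occasions to separate its factors from each other and from measurement error. The primary outcome has assessments before, during and after the intervention. The secondary outcomes have one baseline, nothing during the intervention, then T1 and T2. T3, at 12 months, lies outside the first semester.

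Textbox 1 states hypotheses on mental health and work ability at 6 months against control, and Step 2 calculates effect sizes for the secondary outcomes. Both rely on a model that cannot be fitted in the stated form. The analyst would have to choose restrictions once data are in hand, which is the freedom that publishing the plan was meant to remove.

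**Working it through.** **Inputs.** First-semester occasions, from Outcome Measures and Table 2:
- Fatigue severity: T0a, T0b, M3, M6, M9, T1, T2 = 7. This reproduces the Figure 4 caption ("and 7 indicators Y").
- Other CIS subscales and work ability: T0b, T1, T2 = 3.
- HADS and PANAS: T0a, T1, T2 = 3.

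Times in weeks: end of intervention 9, T1 = 9 + 2 = 11, T2 about 26. The gap from T0a to T0b is not given. I assume 3 weeks; any positive gap gives the same result.

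**Available information.** Three occasions give 3 means and 3 × 4 / 2 = 6 (co)variances per arm. Over three arms that is 9 means + 18 (co)variances = 27 moments.

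**Piecewise model, means.** There are four factors, but a loading matrix with three rows has rank 3 at most.
- Outcomes starting at T0b: S(pre) loads (0, 0, 0). No observation bears on it.
- Outcomes starting at T0a, intercept at T0a: S(pre) loads (0, 3, 3) and S(int) loads (0, 9, 9). The columns are proportional, so the two slopes are collinear.

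Over three arms there are 2 shared means (I, S(pre)) + 3 × 2 free slopes = 8 mean parameters, with rank 7.

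**Piecewise model, covariances.** Per arm there are 4 × 5 / 2 = 10 factor (co)variances plus 1 residual variance (equal over time) or 3 (free), so 11 or 13 parameters. The Jacobian rank is 6. With free residuals over three arms: 8 + 3 × 13 = 47 parameters, rank 25. Moving the second knot from week 9 to T1 changes nothing.

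**Quadratic model.**
- Means: 1 shared intercept + 3 × 2 = 7 parameters, rank 7. Identified, including each arm's mean at T2.
- Covariances per arm: 6 factor (co)variances plus 1 or 3 residual variances = 7 or 9 parameters, rank 6. Not identified.
- Three arms, free residuals: 7 + 3 × 9 = 34 parameters, rank 25. With residuals equal over time and the intercept variance also equal over arms: 26 parameters, rank 25, still one short.

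**Fit comparison.** Drop S(pre) and put time zero at baseline. The piecewise loadings (1, S(int), S(post)) and the quadratic loadings (1, t, t²) are then both invertible 3 × 3 matrices with first row (1, 0, 0). Each gives a common baseline mean and free T1 and T2 means per arm: 7 mean parameters for 9 observed means. The mean structures are equivalent, so fit cannot choose between them.

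**Does the missing restriction matter for the T2 contrast?** Write Σ = ΛΨΛ' + θI, with Λ the 3 × 3 loading matrix, Ψ the factor covariance matrix and θ the residual variance. For any fixed θ below the smallest eigenvalue of Σ, Ψ = Λ⁻¹(Σ − θI)Λ'⁻¹ returns the same Σ. Any such value of θ gives the same likelihood, T2 contrast and standard error; only the reported factor variances move. Two restrictions that identify the quadratic model show the difference:
- Residuals fixed at 0: 7 + 3 × 6 = 25 parameters, rank 25. Σ stays unrestricted, so T2 inference is unchanged.
- Zero factor covariances with equal residuals: 7 + 3 × (3 + 1) = 19 parameters, rank 19. This puts 4 parameters on 6 (co)variances per arm, so Σ is constrained and the standard error can change.

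**The case against.** The strongest reply is that little inference is lost. The confirmatory secondary hypothesis is a comparison of arms at T2, those means are identified in the quadratic model, and a just-identifying restriction leaves the test unchanged. That stands. A reader might infer that the 6-month comparisons cannot be tested at all, or that any restriction would alter their P-values; the algebra supports neither.

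Second, half of the planned runs use time-varying loadings, and Bayesian estimators are mentioned. Spread in individual timings can identify the quadratic variances: with an assumed SD of 1 week the rank rises to 7 of 7 or 9 of 9. That identification is weak. It cannot help S(pre) where its loading is zero for everyone, and the fixed-loading versions are also to be run.

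Third, the article says its plan is written in general terms, and residual restrictions are commonly left to a fuller document. That would answer an omission. Here the article prescribes a procedure, names one exception for these outcomes and leaves out the one that decides whether it can be run.

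A reader might also extend the point to the primary model, since S(pre) is informed by T0a alone. With seven occasions and residual variances free at every occasion, the piecewise model does fall short (rank 16 of 17 per arm, or 15 of 17 with the knot at T1). But the article states no residual structure, and with equal residual variances the model is identified (11 of 11). Nothing is stated wrongly there.

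**Conclusion.** The point holds for the other CIS subscales, work ability, HADS and PANAS. With fixed loadings and random factors, as Table 5 implies, the three-slope piecewise model is not identified even in its means. The quadratic model is identified in its means but not in the variances that Table 5 promises. After S(pre) is dropped, the comparison between the two is uninformative. The four-model procedure therefore cannot be carried out as written for these outcomes.

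The consequence is limited. The T2 contrast is estimable and does not depend on which just-identifying restriction is used. The exposure is to an over-restrictive choice made after seeing data, such as dropping a slope variance, which could change the standard error. How far it would do so cannot be computed from the article, which gives no covariances for these outcomes.

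The result rests on reading the first semester as ending at T2 and on residual variance being part of the model. It does not depend on the assumed T0a to T0b gap. This is a correction worth making before the secondary outcomes are analysed; it does not threaten the primary analysis.

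**What to change.** For the secondary outcomes, replace the four-model procedure with one prespecified model that three occasions can support. One suitable choice is a likelihood-based repeated-measures model with time as categories (baseline, T1, T2) by arm, a common baseline mean and an unstructured covariance matrix, testing each intervention against control at T2. Baseline would be T0a for HADS and PANAS and T0b for the others. If a growth model is preferred, drop S(pre), choose one time form and state the identifying restriction in advance.

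The cost is a change of wording. Individual growth-factor variances would not be reported for the secondary outcomes, but three occasions with fixed loadings cannot supply them anyway. The primary-outcome model stays as it is.
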